#### 8.1.2 Secondary study parameters/endpoints

Secondary outcome measurements are symptom specific and quality of life related questionnaires (PGI-I, EQ-5D-5L and SF-Qualiveen), the amount of urethral damage/strictures and kidney/bladder stone formation. To evaluate if urinary cultures/urinary microbiome changes if a patients is reusing a catheter, the patients will hand in catheterized urinary samples for testing at the two clinical visits.

Furthermore, economical evaluation of the cost-effectiveness of single-use versus reusable catheters will be performed in cooperation with the health economist within our project group, using the iMCQ and iPCQ questionnaires, which will be entered at week 6, week 26 and week 52. The costs of the Cliny catheter set, including the sterilizing solution, will be included in the economical evaluation. Patients perspective on ease of use and cleaning of the reusable catheters compared to the single-use catheters will be evaluated by the ISC-Q, the InCaSaQ and, for the

intervention group, also the PGI-I questionnaire. These questionnaires are developed to investigate difficulties in use, the impact of catheterization on patients and the overall acceptance in patients and will be entered at baseline, week 6, week 26 and week 52. Overall quality of life will be evaluated by the EQ-5D-5L measure method and the SF-Qualiveen and will be entered at baseline, week 6, week 26 and week 52. All used questionnaires are validated in Dutch.

Two additional questions concerning patients thoughts on environmental burden and healthcare costs will be asked at week 0 and week 52.

### **8.1.3 Other study parameters**

Other parameters such as patients characteristics, underlying (immune)diseases, hand function and mobility will be assessed.

## **8.2 Randomisation, blinding and treatment allocation**

Patients who sign informed consent will be randomised into the intervention or in the control group. Randomisation will be performed using the program ALEA, which is the program used in the Erasmus MC. ALEA is developed for randomisation and guarantees concealed allocation. The groups will be stratified for the participating centres, neurogenic and non-neurogenic causes for catheterization, age (16-17 years vs.  $\geq 18$  years and  $< 50$  years vs.  $\geq 50$  years old), gender, and the female patient group will be balanced for pre- and post-menopausal status. There is no ability for blinding in this trial.

## **8.3 Study procedures**

This study will be a prospective non-inferiority trial with two randomized groups. The patients will be screened, included and randomized at the outpatient clinic of the participating hospital departments. One group of patients will use the reusable catheter and the control group will use the single use catheters. After inclusion, the patients will be followed up for a period of twelve months. See chapter 3 'Study design' for the precise follow up schedule.

There will be two extra clinical consults and seven telephone consults when participating in this study. Patients will receive a financial compensation for the expenses of traveling to the hospital for the clinical consultations.

Tracking UTIs and hospital admissions will be performed by status analysis by the researchers of the trial and patients will track their infections using a diary. Active cooperation of the involved consultants and continence nurses is asked when the participating centers are included in the trial. For the contact moments, standardized

questions will be provided in Gemstracker, so all patients will be asked the same questions and data will be as complete and similar as possible.

#### **8.4 Withdrawal of individual subjects**

Subjects can leave the study at any time for any reason if they wish to do so without any consequences. The investigator can decide to withdraw a subject from the study for urgent medical reasons.

##### **8.4.1 Specific criteria for withdrawal**

When it turns out during the trial that a patient is not able to apply the cleaning method the correct way, they will be offered a new schooling moment with a continence nurse. When an incorrect cleaning method is persistent, they will be excluded from the trial, to protect patients' safety.

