#### **8.6 Follow-up of subjects withdrawn from treatment**

When a patient is withdrawn from the trial, regardless of the reason for withdrawal, follow up will be terminated because patients will return to their original single use regime.

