## 4 Trial Population

### 4.1 Screening Data, Eligibility and Recruitment

A CONSORT flow diagram (appendix A) will be used to summarise the number of patients who were:

- assessed for eligibility at screening
- eligible at screening
- ineligible at screening\*
- eligible and randomised
- received the randomised allocation
- lost to follow-up\*
- discontinued the intervention\*
- randomised and included in the primary analysis
- randomised and excluded in the primary analysis\*

\*reasons will be provided.

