### 4.3 Withdrawal/Follow-up

The status of eligible and randomised patients during the trial will be presented in a flowchart according to treatment group.

- completed intervention
- withdrew consent
- lost to follow-up

Time from randomisation to treatment discontinuation and time from randomisation to withdrawal/lost of follow-up will be presented in a table. Information on the number of withdrawals, reasons for withdrawal, and number included in the analysis will be provided.

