#### 4.4.2 Protocol Deviations

The following protocol deviations, which impact the statistical analyses, will result in exclusion from the Per-Protocol Set (PP):

- Entering the trial when the eligibility criteria should have prevented trial entry
- Discontinuation of intervention prior to 52 weeks
- Use of single-use catheters in more than 20% of catheterizations in the intervention arm
- A new onset exclusion criterium.

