## 4.5 Analysis Populations

The Enrolled set will include all patients who have provided informed consent and have been included into the study data base.

The intention-to-treat (ITT) analysis set will include all patients randomly assigned to a treatment group, who started with the treatment, regardless of whether they completed the treatment or adhered to the protocol.

The modified intention-to-treat (mITT) analysis set will include all patients who were randomly assigned to a treatment group with at least 6 weeks of follow-up data (i.e., those who attended the first clinical follow-up visit).

The Per Protocol (PP) Analysis Set will include all randomised patients meeting the study eligibility criteria who completed the 52 weeks follow-up. (i.e., those who attended the final study visit).

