## 6.1.2 Primary Analysis

For the primary outcome, the incidence rate in each group is the total number of UTIs divided by the total follow-up time, reported with 95% confidence intervals calculated using bootstrap procedure. The absolute difference between groups will be calculated and reported with a 95% bootstrap confidence interval. Non-inferiority will be concluded if the upper limit of the CI is below the non-inferiority margin of 7%. The incidence rate ratio (IRR) with a 95% CI will be estimated in both arms using a poisson or negative binomial regression model (in case there is overdispersion of the data). All analyses will be conducted using R version 4.2.1 (R Foundation for Statistical Analysis, Vienna, Austria).

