## 6.1.3 Missing Data

For the primary analysis missing data will not be imputed.

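### Patients removed for persistent cleaning failure, possible only in the reusable arm, are not followed further, so the ITT set lacks their later UTIs and the bias has no known sign or size

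*Combined protocol and SAP*

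**What the plan says.** - **Exclusion.** Protocol 8.4.1 offers a patient who cannot clean correctly another session with a continence nurse. If that fails: "When an incorrect cleaning method is persistent, they will be excluded from the trial, to protect patients' safety". Protocol 13.2 repeats the rule and mentions a high chance of infection in these patients.
- **End of follow-up.** Protocol 8.6, for every withdrawal: "regardless of the reason for withdrawal, follow up will be terminated because patients will return to their original single use regime".
- **Analysis set.** SAP 4.5 keeps in the ITT set all randomised patients who started treatment, "regardless of whether they completed the treatment or adhered to the protocol".
- **Estimator.** SAP 6.1.2: "the incidence rate in each group is the total number of UTIs divided by the total follow-up time". Non-inferiority needs the upper 95% limit for the difference to lie below 7%, that is 0.07 UTI per month.
- **Missing data.** SAP 6.1.3: "For the primary analysis missing data will not be imputed".
- **Per-protocol set.** SAP 4.4.2 removes patients with "Discontinuation of intervention prior to 52 weeks".
- **Reporting.** The flow diagram in SAP 4.1 counts patients who "discontinued the intervention" separately from those lost to follow-up, with reasons. SAP 4.3 adds: "Time from randomisation to treatment discontinuation and time from randomisation to withdrawal/lost of follow-up will be presented in a table".

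**The concern.** Taking the reusable catheter away after failed re-schooling is a sound safety rule. The difficulty is that the patient also leaves the trial. Control patients have nothing to clean (SAP 4.4.1 forbids them to reuse), so this exclusion can occur in one arm only. It also selects on a factor that Protocol 11.4 and 13.2 link to infection risk.

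For these patients the ITT analysis becomes an on-treatment analysis. Their UTIs before exclusion count; everything after is absent from both numerator and denominator. The per-protocol set drops them by design. The tables in SAP 4.1 and 4.3 would show how many were lost and when, but cannot recover the events, and for this group the stop date and the end of follow-up coincide.

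In a non-inferiority trial, a reusable-arm rate that is too low makes the claim easier to reach. Whether it is too low depends on a rate that nobody will have measured.

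**Working it through.** **The plan's own figure.** Protocol 4.4 uses SD 0.21, one-sided alpha 0.025, power 0.80 and a margin of half the mean rate, 0.5 × 0.135 = 0.0675. Then n = (1.960 + 0.842)² × 2 × 0.21² / 0.0675² = 151.9, so 152 per arm as stated. (The rounded margin 0.07 would give 142. Dividing 152 by 0.80 gives 190 per arm; the plan states 191.)

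**Inputs from the documents.** Monthly rates 0.13 (single-use) and 0.14 (reusable); 12 months of follow-up; 193 per arm; cleaning checked at weeks 6 and 26.

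**Assumptions, because the documents give none.** Share of the reusable arm excluded w = 5% or 10% (10 or 19 of 193). Exclusion about two weeks after a check: week 8 (t = 1.846 months) or week 28 (t = 6.462). Rate before exclusion r = 0.14, 0.28 or 0.42. Rate after exclusion r2 = r or 0.13.

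**Formulas.**
- Observed reusable rate R = [(1−w)·12·0.14 + w·t·r] / [(1−w)·12 + w·t]
- Rate with full follow-up F = [(1−w)·12·0.14 + w·(t·r + (12−t)·r2)] / 12
- Bias in the ITT difference = R − F. A negative value favours non-inferiority.

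**If the raised rate persists (r2 = r).**

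| w | r | Difference, week 8: plan / full | Bias, week 8 | Bias, week 28 |
|---|---|---|---|---|
| 5% | 0.28 | 0.0111 / 0.0170 | −0.0059 | −0.0031 |
| 5% | 0.42 | 0.0122 / 0.0240 | −0.0118 | −0.0063 |
| 10% | 0.28 | 0.0124 / 0.0240 | −0.0116 | −0.0061 |
| 10% | 0.42 | 0.0147 / 0.0380 | −0.0233 | −0.0122 |

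With r = r2 = 0.14 the bias is zero.

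**If the rate falls to 0.13.** Bias is +0.0004 to +0.0012 for week 8 and +0.0002 to +0.0012 for week 28.

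**Where the sign changes.** R = F exactly when r2 = R: at 0.140-0.145 for week 8 and 0.140-0.156 for week 28. The plan's two rates, 0.13 and 0.14, lie at or just below these values, so a modest rise after exclusion is enough to turn the sign.

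**Tipping point (approximate; SE held fixed, r = 0.14, exclusion at week 8).** With 152 per arm the half-width is 1.96 × 0.21 × √(2/152) = 0.0472. A difference of 0.010 gives an upper limit of 0.0572. The missing share of reusable person-time is w(12−t)/12 = 0.0846 (10%) or 0.0423 (5%). To reach 0.07, the missing months need a rate of:
- 10%: 0.14 + 0.0128/0.0846 = 0.29, or 2.1 times 0.14
- 5%: 0.14 + 0.0128/0.0423 = 0.44, or 3.2 times
- with 193 per arm (half-width 0.0419): 0.35 (2.5 times) and 0.57 (4.1 times).

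**The case against.** The strongest reply is that the documents' own mechanism makes the bias harmless. Faulty cleaning raises risk, the patient returns to single-use, the cause is gone, and the bias is then at most +0.0012, under 2% of the margin and conservative. The unfavourable figures need a raised rate to outlast its stated cause, and nothing in the documents says that it would. This stands as far as it goes. But no passage says that the rate returns to 0.13 either, and patients who fail at cleaning may differ in other ways.

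Second, the documents do not say which question is meant. For risk on the reusable device, stopping at discontinuation is defensible, and following patients on single-use would not answer that question. Read that way, 13.2 does point in one direction: any rate above 0.14 under faulty cleaning makes the observed rate too low, by the amounts in the table. The statement that the sign is unknown applies to the ITT comparison that SAP 4.5 defines. SAP 6.1.2 does not name the set for the primary analysis, which is a separate gap.

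Third, follow-up on single-use can dilute a true difference. At 10% excluded at week 8, 3 times the rate before and 0.13 after, it gives 0.0135 against 0.0147 under the current plan. This is correct, and is why an on-treatment result belongs beside it.

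Fourth, the assumed size may be generous. Patients are trained and already self-catheterise, and 10% would be half of the 20% dropout allowance. At 2% excluded at week 8, the tipping rate is 0.14 + 0.0128/0.0169 = 0.90 per month (6.4 times). The plan's formula also assumes no true difference; starting from zero with both arms at 0.13, the tipping rates become 0.40 (3.1 times) at 10% and 0.67 (5.1 times) at 5%. These points reduce the likely size but do not close the gap.

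**Conclusion.** The concern holds. The plan defines an ITT set that its follow-up rule cannot fill, and the shortfall from cleaning failure can arise in the reusable arm only. For the ITT comparison the documents fix neither the sign nor the size of the bias.

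Under the stated assumptions it runs from 0.023 UTI per month in favour of non-inferiority, a third of the margin, to 0.0012 against it. The unfavourable end needs 10% excluded early and a threefold rate that persists; a return to 0.13 makes the matter negligible. With few cleaning failures the conclusion is unlikely to change. The amendment should still be made, because the deciding rate is cheap to collect and cannot be reconstructed reliably afterwards. Confidence is moderate, since the share excluded and both rates in these patients are assumed.

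**What to change.** 1. **Protocol 8.4.1:** have the patient stop the reusable catheter and return to single-use, instead of leaving the trial.
2. **Protocol 8.6:** for any patient in either arm who stops the allocated catheter, continue the scheduled contacts, diary and record review for UTIs to week 52 unless consent is withdrawn. Applying it to both arms keeps ascertainment symmetric. Count these UTIs and months in the ITT analysis, and show alongside it an on-treatment result cut at the stop date.
3. **SAP 6.1.3:** for patients whose follow-up has already ended, add one sensitivity analysis that fills the missing reusable-arm months at 1, 2 and 3 times the reusable-arm rate. For cleaning failures at week 8 with a rate of 0.14 before exclusion, the differences would be 0.0100, 0.0159 and 0.0218 (5%) or 0.0100, 0.0218 and 0.0337 (10%). The 1-times fill leaves the estimate unchanged by construction.
4. **SAP 4.1 and 4.3:** list cleaning failure as its own withdrawal reason; numbers, reasons and timing are already planned.

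**Cost.** A minor amendment with no new visit types. Six contacts remain after week 8 (weeks 12, 18, 26, 34, 42 and 52), so 10-19 cleaning failures mean 60-114 contacts. As an upper limit, if the whole dropout allowance (386 − 2 × 154 = 78 patients) stopped at about week 8 and all agreed, that is 78 × 6 = 468 of the 386 × 8 = 3,088 post-baseline contacts already scheduled. Some patients will decline.

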#### **8.5 Replacement of individual subjects after withdrawal**

There will be no replacement after withdrawal.

#### **8.6 Follow-up of subjects withdrawn from treatment**

When a patient is withdrawn from the trial, regardless of the reason for withdrawal, follow up will be terminated because patients will return to their original single use regime.

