### 4.4 Sample size calculation

The number of studies that have investigated the effects of single use and disposable catheters is limited. Our initial sample size calculation was based on data from a Cochrane review by Prieto et al. (2015), which was later found to contain inaccuracies in

data selection and extraction (9). Specifically, six of the eight trials included in the review did not contain consistent or accurate data compared to their originally published versions. Unfortunately, these erroneous data were used as the basis for our initial sample size calculation ( $n=456$ ). We were therefore required to perform a new sample size calculation based on the revised 2021 Cochrane review with corrected data (14). The revised Cochrane review included ten studies comparing single-use catheters to reusable catheters. To prevent confounding effects related to insertion techniques (clean vs. sterile), six of these studies employed the same insertions method in both study arms. Among these, three studies provided usable data regarding the number of sUTI events in each group. For single use 18 events out of 68 were observed, for reusable 20 events out of 69. This leads to the proportions of 0.26 and 0.29. Further we applied a power of 0.80 and a one-sided alpha of 0.025 (it is customary to adjust one-sided alphas to the half of 0.05). In our previous calculation, the non-inferiority margin had been determined based on 50% of the mean proportions, following the recommendation of Althunian et al. (15) However, with the corrected data, this would have resulted in an increase in the non-inferiority margin to 14%. As this was deemed inappropriate, we opted to maintain the margin at 11%. The sample size is then calculated with:  $n = ((Z(1-\alpha) + Z(1-\beta))^2 [ps(1-ps) + pe(1-pe)]) / ((ps-pe-d)^2)$ , the formula developed by Blackwelder et al in 1982 (16), leading to 154 effective cases in each group. Anticipating a dropout of 20% (17), this must be divided by 80% and rounded upwards. This results in 2 times 193 participants, a total of 386.

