Because the lack of comparable non-inferiority designed trials with the same primary outcome measurement (sUTI) it is chosen to look at non-inferiority trials with a primary outcome measurement of (treatment of) sUTI. All these trials handled a non-inferiority margin of 10% (18) (19-22), and two trials even 15% (23, 24). The head researchers and clinicians of the departments of urology and medical microbiology agreed on the 11% margin to be clinical acceptable.

In addition, we encountered the unique challenge of conducting a study with a significantly extended follow-up period of one year, in contrast to the previous studies used in the sample size calculation above, with a shorter follow-up of 2-4 months. Recognizing the impact of time on the occurrence of urinary tract infections (UTIs) and the need to account for this extended observation period, we also performed a sample size calculation that considered the monthly UTI rates observed by Vapnek et al. (25) This calculation factored in not only the proportion of UTIs but also the temporal aspect, recognizing that the incidence of UTIs may vary over time. Vapnek et al. found that single-use catheters had

an average of 0.13 UTIs per month (SD 0.18) and multiple-use catheters had an average of 0.14 UTIs per month (SD 0.21) per patient (25). We applied the same power of 0.80 and an one-sided alpha of 0.025. A non-inferiority margin of 7% has been determined based on 50% of the means following the recommendation of Althunian et al. (15) We used the most conservative standard deviation of 0.21 and the sample size calculation was performed using the formula developed by Julious:  $n = f(\alpha, \beta) \times 2 \times \sigma^2 / d^2$  (26). This calculation led to a requirement of 152 effective cases in each group. Anticipating a dropout rate of 20%, this figure was divided by 0.80, resulting in a total sample size of 382 participants (191 in each group). Since the sample size of 382 is almost equal to our sample size that does not correct for time (n=386), we will include 386 participants to account for both methods.

Sample size: 386 patients.

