### 5.3.7 Cost-effectiveness

The cost-effectiveness analysis (CEA) of reusable catheters versus single-use catheters will evaluate the incremental costs and incremental health effects of using reusable catheters, with health effects expressed in quality-adjusted life-years (QALYs). This analysis will follow the Dutch health economic guidelines (4) and be conducted by the Institute for Medical Technology Assessment (iMTA) at Erasmus University, Rotterdam. As such the societal perspective will be adopted, meaning that all costs and effects will be included in the analysis, regardless to whom they accrue. The time horizon

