# STATISTICAL ANALYSIS PLAN for COMPaRE-trial

of the cost-effectiveness study will be equal to the timeframe of the clinical trial. Uncertainty concerning the incremental cost-effectiveness ratios, QALYs and costs will be assessed using bootstrapping, and this uncertainty will be presented graphically with the CE-acceptability curve. Data on medical healthcare utilisation (ie, volumes) will be collected both through hospital records and by means of the iMTA Medical Consumption Questionnaire (5). Data on productivity losses will be collected by means of the iMTA Productivity Costs Questionnaire (6). We will use a willingness to pay (WTP) threshold of €20 000/QALY, based on the reference value for cost-effectiveness determined by the National Healthcare Institute of The Netherlands (4). A study on health-economic burden of urinary-catheter-associated infection in England used a similar WTP threshold of £20 000/QALY based on the National Institute for Health and Care Excellence guidelines (7,8). Cost-effectiveness analysis will be presented in separate manuscript.

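### Follow-up stops at withdrawal, and the plan has no rule for the incomplete 52-week costs and QALYs that result

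*Combined protocol and SAP*

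**What the plan says.** **End of follow-up.** Protocol 8.6 applies to every withdrawn patient and gives its reason: "follow up will be terminated because patients will return to their original single use regime". The heading of 8.6 speaks of withdrawal from treatment and its text of withdrawal from the trial, so the two are not kept apart. Section 8.4.1 excludes patients whose cleaning stays incorrect after retraining, and 8.5 allows no replacement.

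**Planned dropout.** Protocol 4.4: "Anticipating a dropout of 20% (17), this must be divided by 80% and rounded upwards".

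**Economic analysis.** SAP 5.3.7 adopts the societal perspective, under which "all costs and effects will be included in the analysis, regardless to whom they accrue". Protocol 10.2 schedules the EQ-5D-5L at weeks 0, 6, 26 and 52, and the iMCQ and iPCQ at weeks 6, 26 and 52. The SAP also fixes the period to be covered, since the horizon "of the cost-effectiveness study will be equal to the timeframe of the clinical trial". The SAP's overview of outcomes lists QALYs and total costs as secondary outcomes. Bootstrapping is the method named for uncertainty, and the willingness-to-pay threshold is EUR 20,000 per QALY.

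**Missing data.** The SAP rules out imputation for the primary outcome (6.1.3), adverse events (6.1.4.2), patient opinion (6.2.2.2) and urine cultures (6.2.3.2). Questionnaire scores, including the EQ-5D-5L, get a linear mixed model under missing at random (6.2.1). No rule is given for costs or QALYs.

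**The concern.** A 52-week cost or QALY needs information to week 52. Under 8.6, a patient who leaves at month 5 supplies no later utility, care use or productivity data, yet the stated horizon still covers months 5 to 12. The SAP does not say how that gap is to be filled, or which patients the cost and QALY means are taken over.

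The gap also differs between arms. A control patient who withdraws goes on with the same kind of catheter. A reusable-arm patient who withdraws changes back to single-use catheters, and under an allocated-arm comparison that later cost and quality of life belong to the reusable strategy. Incorrect cleaning, a withdrawal ground that can arise only in the reusable arm, removes patients in whom reuse did not work. Cost saving is part of the trial's rationale (Protocol 1) and cost-effectiveness is a stated objective (Protocol 2), so a loss tilted towards apparent saving matters.

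**Working it through.** **Inputs.** Evaluable patients per arm: 154 (Protocol 4.4). Dropout: 20% (Protocol 4.4, assumed at planning). Questionnaire weeks: Protocol 10.2. The timing of withdrawal is not given, so it is assumed below.

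**1. The plan's own figure.** 154 / 0.80 = 192.5, rounded up to 193 per arm, and 2 × 193 = 386. This agrees with the plan: "This results in 2 times 193 participants, a total of 386".

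**2. Patients without a complete 52-week total.** 0.20 × 386 = 77.2, about 77 in both arms together (by the plan's rounding, 386 − 2 × 154 = 78). In the reusable arm, 0.20 × 193 = 38.6, about 39.

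**3. How much of the year is unobserved.** If withdrawals were spread evenly over 52 weeks (assumed):

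- before week 6: 77.2 × 6/52 = 8.9
- weeks 6 to 26: 77.2 × 20/52 = 29.7
- after week 26: 77.2 × 26/52 = 38.6

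Most of the 77 would therefore have some post-baseline data. Unobserved time is 77.2 × 0.5 = 38.6 of 386 patient-years, or 10%. If all left at week 6 it would be 77.2 × (46/52) / 386 = 17.7%.

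**4. Effect on the catheter saving if only completers were used.** Let S be the catheter saving per patient over a full year on the reusable catheter, and w the share of the reusable arm that reverts at mid-year. A reverting patient saves for half the year, so the all-randomised saving is S × (1 − 0.5w). A completer analysis gives S. The overstatement is 1/(1 − 0.5w) − 1, and the price of the reusable set cancels out.

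| Dropout (assumed) | Both arms | Reusable arm | All-randomised saving | Overstatement |
|---|---|---|---|---|
| 10% | 39 | 19 | 0.95 S | 5% |
| 20% | 77 | 39 | 0.90 S | 11% |
| 30% | 116 | 58 | 0.85 S | 18% |

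With 20% all reverting at week 6, the saving is (1 − 0.20 × 46/52) S = 0.823 S, an overstatement of about 21%. In every case the factor is positive, so the sign of the saving does not change.

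**5. Do other parts of the plan close the gap?**

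- Bootstrapping describes sampling uncertainty in totals that exist; it does not create missing ones.
- The mixed model in SAP 6.2.1 includes the EQ-5D-5L, but no step leads from it to QALYs, and the iMCQ and iPCQ are not in its list. With nothing observed after withdrawal, it projects from patients still in follow-up.
- Protocol 10.2 allows hospital records for consultations and admissions for symptomatic UTIs. They give no utilities or productivity loss, and 8.6 provides for no collection after withdrawal.
- The ITT set in SAP 4.5 keeps starters who did not complete, but the economic section does not refer to it, and it adds no data.

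**The case against.** The strongest reply is that much of this can be recovered. Withdrawn patients keep every questionnaire completed before they left. The EQ-5D-5L, the only utility source, already has a missing-at-random model, and hospital records are a second source for UTI care. Catheter cost after withdrawal can be priced without further contact: 8.6 states the regime, SAP 4.3 tabulates time to discontinuation, and Protocol 10.2 takes catheter prices from the hospital administration. The analysis is assigned to a health technology assessment institute under Dutch guidelines, for a separate paper, and may well handle missing data properly.

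Much of that stands, and it limits what can be claimed. A reader might infer any of the following, and the documents do not support them:

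- *The 77 patients cannot be scored.* They have partial data; they lack a complete observed total and a stated rule.
- *The cost after withdrawal is lost.* The catheter part can be reconstructed. Later care use outside hospital records, productivity and utility are what go unobserved.
- *The ICER will be based on completers.* No section says so. It is one possible default when nothing is specified.
- *All 77 bear on the cost of the reusable strategy.* About 39 do.
- *The full price of single-use catheters after reversion is the bias.* That is a gross figure. The completer mean already contains the reusable cost, so the error is a fraction of the net saving, as in step 4.

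What does not stand is the suggestion that nothing needs to change. The end of follow-up in 8.6 is a stated rule, and no later analysis can recover data that were never collected. SAP 5.3.7 already fixes the perspective, horizon, bootstrap and threshold, so the analysis set and missing-data method belong there too.

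**Conclusion.** The point holds in this form. Protocol 8.6 conflicts with a societal, full-year economic analysis, and the SAP does not say how incomplete costs and QALYs will be handled. At the planned 20% dropout, about 77 of 386 patients (about 39 in the reusable arm) would lack a complete observed 52-week total. The loss is tilted because reversion changes the strategy's cost only in the reusable arm, and one withdrawal ground exists only there.

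The size is moderate. The catheter saving would be overstated by about 11%, with a range of 5% to 18% for 10% to 30% dropout. This rests on three assumptions: a completer analysis, reversion at mid-year on average, and the planning dropout applying equally to the reusable arm. The effect on care use, productivity and utility cannot be sized from the documents. Nothing shows that the conclusion at EUR 20,000 per QALY would move. The matter concerns secondary outcomes and should be settled before database lock.

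**What to change.** **Protocol 8.6.** Separate stopping the allocated catheter from withdrawing consent. For patients who stop the catheter and agree, keep sending the week 6, 26 and 52 EQ-5D-5L, iMCQ and iPCQ through the existing email system, and keep using hospital records. The criteria for stopping the catheter need not change, and the sample size stays at 386.

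**SAP 5.3.7.** State that:

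- costs and QALYs are analysed in all randomised patients by allocated arm;
- catheters after reversion are priced at the single-use price from the recorded discontinuation date;
- remaining gaps are handled by a pre-specified missing-at-random method, for example multiple imputation by arm combined with the bootstrap (other methods would also serve);
- a completer analysis and an analysis allowing for non-random missingness are reported as sensitivity analyses.

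**Cost.** A protocol amendment, SAP text and some programming; the questionnaire emails already exist. The main result will lean on an imputation model. Patients who withdraw consent or are lost will still supply nothing after they leave, and the change to 8.6 helps only those who have not yet reached week 52.
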